# Patients with lumbar spinal stenosis who will undergo uniportal endoscopic decompressive laminectomy

- Target sample size: 120 subjects (Study group: 60 subjects, Control group: 60 subjects, including 20 % drop-out rate)
- Primary outcome: ODI (Oswestry disability index)
- According to a previous study [1], the MCID (Minimal clinical important difference) of ODI was 12.8 and in another previous study [3], the standard deviation of the ODI value at 1 year after decompressive laminectomy was 18.8. Assuming an equivalence limit of 12.8, under the conditions of alpha = 0.05, power = 0.90, two-sided 95% confidence interval, and follow-up loss at 20%, 60 participants are needed in each group.

[figure not shown]

Subject Recruitment Plan

This is a prospective, multicenter study which will recruit subjects at the Department of Neurosurgery of Seoul St. Mary’s Hospital, Chundam Woorideul Spine Hospital and the Wiltse Memorial Hospital (Anyang). Those who are planning to undergo one-segment or two-segment decompression surgery for lumbar spinal stenosis will be recruited as subjects and advertisement for subject recruitment will not be used.

The surgical method investigated in this study is the most commonly used technique for lumbar spinal stenosis, and the clinical study is conducted through pre- and post-operative surveys and analysis of clinical and imaging data, so there is no harm to the subjects. However, if the subject refuses to participate in the study, the trial will not proceed with the subject. In addition, although this study is conducted on a patient group, there is no obligation or undue influence for participation, and there is no disadvantage to the patient for not participating in the study. Among those who voluntarily agreed to participate in this study and signed an informed consent form (ICF), those who met the inclusion criteria for this study and were not applicable to the exclusion criteria were selected, and subjects were randomly assigned to either of the study or control groups. The Principal Investigator (PI) of this study will not exclude subjects who are likely to participate in this study based solely on race or socioeconomic status. As long as the subject is eligible in terms of inclusion/exclusion criteria, the PI will make every effort to encourage the subjects to participate in the study, and inform the subjects of the objectives of this study so that they can properly represent the total of the patients who will undergo the treatment.

Assessment and Analysis of Study Results and Items for Observation

- **Demographic information:** Age, gender, and date of surgery of subjects

– **Physical examination and basic tests:** Medical history, smoking habits, basic blood tests, physical examination

– **Radiological tests:** The subjects undergo simple radiography and MRI (or CT) examination for baseline assessment. After surgery, during the hospitalization period, the degree of canal release, complications, and recurrence are examined through simple radiography and MRI (or CT) scans.

- **Oswestry disability index (ODI) questionnaire:** Scoring of the Oswestry disability index (10 items) is conducted at the visit. The investigator hands out the subject a questionnaire, and asks the subject to rate each item on a five-point scale for self-report. The rated score is expressed as a percentage of the total score of the answered questions excluding the questions not completed by the subject.

- **EQ5D-5L questionnaire:** The EQ5D-5L questionnaire (5 items) is conducted at the visit. The investigator hands out the subject a questionnaire and asks the subjects to rate and indicate each item for self-report. The total score of the indicated items is converted using the EQ5D value set for calculation.

- **VAS score ( pain scale):** The degree of pain felt by the subject during activity is assessed using a 100mm VAS (Visual Analogue Scale) for both lower back and the legs. The investigator explains the VAS to the subject and asks the subject to rate each item and indicate accordingly for self-report. In addition, the degree of pain in the surgical site (Postoperative Day 1 or Day 2) is also investigated using VAS.
- **Walking time:** The changes in values in the questions on walking ​​at postoperative 2, 12, 24, and 52 weeks are compared to the baseline values.
- **Satisfaction after surgery:** At the 1-year follow-up visit, the investigator hands out the questionnaire to the subject and asks the subjects to indicate for self-report.
- **Return to daily activities after surgery:** The time required to return to daily activities postoperatively (week)
- **Scar after surgery (POSAS[Patient and Observer Scar Assessment Scale] patient scale 2.0):** The patient assesses the postoperative scarring with 6 items and scored on a ten-point system, with a score of 1 indicative of normal skin and a score of 10 indicative of the worst scar imaginable, and the total score of the assessment is 60.

- **Other surgery-related outcomes:** The size of the surgical skin incision, postoperative drainage, operative time, duration of hospitalization (hours), postoperative Day 1 creatine kinase (CK, CPK) are also evaluated.

- **Presence of adverse events and complications:** Adverse events requiring revision surgery related to the intervention. When a patient arrives at the ward after completing the surgery, a resident (or fellow, clinical instructor, nurse, investigator, etc.) who is blinded to the surgical method examines the patient to determine whether there are any complications related to the intervention or any serious complications that require revision surgery.

Efficacy Assessment Criteria, Assessment Method, Interpretation

1. Primary Endpoint

The primary endpoint of this trial is the difference between the ODI score measured at baseline and that measured 12 months postoperatively.

Statistical analysis method: Equivalency will be declared if the upper and lower limits of the 95% confidence interval (CI) of the treatment difference value of each group’s ODI score at 12 months postoperatively fall within the pre-defined equivalence margin (+-12.8).

1. Secondary Endpoints

The secondary endpoints for this trial include clinical outcomes (VAS, EQ5D-5L, ODI, walking distance and time, satisfaction after surgery, time required to return to daily activities postoperatively, POSAS), radiographic outcomes, and other surgery-related outcomes.

Statistical analysis method: For each group, the differences from the baseline values to the postoperative values and differences in the pattern of change between the two groups are analyzed using repeated measures analysis of variance (ANOVA). In addition, for specific within-group or between-group comparisons at each time point, the t-test is used, while applying the adjusted significance level considering the multiplicity of the test.

Satisfaction after surgery, time required to return to daily activities postoperatively, Patient and Observer Scar Assessment Scale(POSAS scale)

Statistical analysis method: The satisfaction after surgery, the time to return to daily activities postoperatively, and POSAS scale score at the time of final postoperative follow-up are comparatively analyzed between the two groups using the t-test.

- Radiographic outcomes

Examination of the occurrence of complications during the final follow-up using simple radiographs (Development of spondylolisthesis, progression of degenerative lumbar spinal conditions, etc.), analysis of surgical outcomes through postoperative MRI (or CT)

- Statistical analysis method: The occurrence of complications is examined for each group, and Chi- square test or t-test is used for comparative analysis on the difference between the two groups for the degree of central canal release and the canal dimension measured using postoperative MRI or CT.

- Other surgery-related outcomes

Comparison between the two groups on other surgery-related outcomes. [size of the surgical skin incision, postoperative drainage, operative time, duration of hospitalization (hours), Postoperative (From immediately after surgery to discharge from the hospital), postoperative Day 1 creatine kinase (CK, CPK)]

Statistical analysis method: The degree of difference between the two groups is evaluated using the chi-square test or t-test.

General Statistical Analysis

General principles of analysis

- For continuous variables, descriptive statistics (number of subjects, mean, standard deviation, median, minimum, maximum) are presented, and for categorical variables, frequency (N) and percentage (%) are presented.

- In the analysis of the primary efficacy endpoint, if missing data occurs due to dropout, etc., the data are processed as a failure and the non-responder imputation (NRI) method is used.

- If the clinical trial is discontinued according to the discontinuation criteria, the data are handled as missing values.

- In the analysis of secondary efficacy endpoints, when there are missing values in the data, a method of last observation carried forward (LOCF) is used.

- For the analysis of the safety set, when there are missing values in the data, the data shall be analyzed as it is without performing imputation for the missing values (OC method).

Handling of analysis sets

- The analysis sets are categorized into safety set, full analysis set (FAS) and per protocol (PP) set.

- Efficacy data are analyzed using both FAS and PP, and final determination on efficacy endpoints is conducted by FAS analysis based on the modified ITT (intention to treat).

- Data on safety are analyzed for the safety sets.

- For the analysis of efficacy endpoints, when there are missing values in the data, the data shall be analyzed as it is without performing imputation for the missing values.

Definition of analysis sets

• FAS (Full Analysis Set): Subjects who met the inclusion/exclusion criteria and who underwent randomization to receive the intervention at least once during the trial period are included in FAS. In the efficacy analysis, regardless of the actual status of undergoing the surgery, analysis is performed based on the treatment group assigned by randomization.

• PP (Per Protocol Set): Subjects who have completed the trial without major protocol violations among the full analysis set (FAS) are included in PP set. However, if the trial is discontinued according to the discontinuation criteria, the clinical trial is considered to be completed and included in the PP analysis. For items of major protocol violations, see Section 13-5.

• Safety Set: Subjects who were randomized and have undergone the surgery at least once during the trial period are included in the safety set. In the safety analysis, analysis is performed based on the classification according to the actual type of surgery received.

|  | | | | | | |
| --- | --- | --- | --- | --- | --- | --- |
| **Patient Evaluation:**  **Schedule of Activities** | | | | | | |
| **Visit Type** | **Screening** | **Operation/**  **Treatment** | **Follow-up** | | | |
| **Visit** | **1** | **2** | **3** | **4** | **5** | **6** |
| **Visit week** | **-4~0weeks** | **0 day** | **2 weeks** | **12 weeks** | **24 weeks** | **52 weeks** |
|  |  |  | **± 5 days** | **± 4 weeks** | **± 8 weeks** | **± 8 weeks** |
| Subject written consent | ■ |  |  |  |  |  |
| Demographic information | ■ |  |  |  |  |  |
| Medical history/Surgical history^[1]^ | ■ |  |  |  |  |  |
| Physical examination | ■ |  |  |  |  |  |
| Clinical laboratory tests^[2]^ | ■ |  |  |  |  |  |

| Inclusion/Exclusion criteria | ■ | ■ |  |  |  |  |
| --- | --- | --- | --- | --- | --- | --- |
| Randomization |  | ■ |  |  |  |  |
| Surgery |  | ■ |  |  |  |  |
| MRI or CT | ■ | ■ |  |  |  |  |
| X-ray^[4]^ | ■ |  | ■ | ■ | ■ | ■ |
| ODI questionnaire | ■ |  | ■ | ■ | ■ | ■ |
| EQ-5D questionnaire | ■ |  | ■ | ■ | ■ | ■ |
| VAS questionnaire | ■ |  | ■ | ■ | ■ | ■ |
| Walking questionnaire |  |  | ■ | ■ | ■ | ■ |
| Other questionnaire^[5]^ |  |  | ■ | ■ | ■ | ■ |
| Collection of adverse events |  | ■ | ■ | ■ | ■ | ■ |
| * Visit 1 and visit 2 may proceed concurrently.   1. Investigation of medical history within 3 years from the time of screening (5 years in case of cancer) 2. Laboratory tests:   - Hematology (CBC): WBC, Hb, Hct, ESR - Biochemical profile (routine chemistry): hs-CRP, CPK   1. Simple radiography (X-ray): Simple radiographs will be obtained in the anteroposterior (AP), lateral, lateral-flexion, and lateral-extension views. In order to prevent undergoing excessive radiographic examinations, it is possible to replace the examination results with those taken within 4 weeks from the date of screening or follow-up visit. 2. Other questionnaires: satisfaction with the surgery, daily activities, POSAS scar questionnaire | | | | | | |

Expected Adverse Events/Risks and Countermeasures

The posterior spinal decompression surgery to be performed in this trial is a standard treatment for patients with lumbar spinal stenosis. There are no additional complications specifically from this study other than those related to general spinal surgery.

However, if AEs related to this clinical study occur, the investigator will take the following actions:

1. The investigator will immediately report to the IRB upon discovering the adverse event.
2. The investigator will take necessary medical action.

If the subject requires emergency measures due to this study, the necessary emergency measures shall be taken as soon as possible. In addition, in the case of serious adverse events (SAEs), prompt and appropriate actions shall be taken to minimize possible damage. However, general complications expected after lumbar spinal surgery are not considered as complications “caused by this study.”

* Discontinuation•Drop-out Criteria

The principal investigator may consider discontinuation of the clinical study in the following cases.

1. In the event of serious adverse events (SAEs) in subjects
2. Other cases where the investigator deems that continuation of the study may be difficult

The cases for consideration of subject dropout are as follows.

1. Non-compliance to the instructions of the investigator
2. If the subject or LAR withdraws the consent to participate (presented explicit wishes to refuse the participation in the study)
3. Violation of the inclusion/exclusion criteria
4. In the event of serious adverse events SAEs/adverse device effect (ADE)
5. Other cases where the investigator deems that continuation of the study may be difficult

In the event of a withdrawal or dropout of a subject, the investigator must make every effort to follow-up the study subject who has withdrawn or dropped out for any reason, and must perform a follow-up monitoring evaluation for safety.

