**Assessment Criteria, Assessment Method and reporting of Safety, including Adverse Events**

Adverse events occurring during the clinical trial are followed up until the symptoms are resolved or stabilized. Adverse events that occur are coded using Preferred Terms (PTs) according to the Medical Dictionary for regulatory activities (MED-DRA). All adverse events (AEs) and serious adverse events (SAEs) that occurred after treatment and the unexpected adverse events (UAEs) related to the treatment in the trial are summarized according to the severity by the time point of onset using Preferred Terms (PTs) and prepared in graphs. These are recorded based on the self-report of the subjects and examination during their visits. In recording the AE-related information, the name and duration, the scope and severity of symptoms, the causal relation with the medical device, additional treatment, the outcome of AEs, and the status of seriousness are described in detail in the Special Form of the case report form (CRF).

Statistical analysis method: In this study, AEs indicate cases of new or worsened symptoms or signs that were not observed during the baseline assessment and include all signs, symptoms and diseases regardless of the causal relation with the medical device. In the event of AEs, the name of the related symptoms, time of onset, duration, severity of symptoms, and causal relation with the investigational device are recorded in CRF. The number of cases and the number of applicable subjects are calculated for each case of AEs, and the rate of occurrence of adverse events 95% two-sided confidence intervals are presented. The difference in the rate of AE occurrence between the two groups is compared using the chi-square test or Fisher's exact test.

Protocol Abstract(cont'd)

Estimated Accrual:

Target sample size 120 subjects (Study group 60 subjects, control group 60 subjects, including 20% drop-out rate)

Phase:

□ Phase I □ Phase IIa □ Phase IIb □ Phase III □ Phase IV □ Phase I/II ■ Other

Site of Study:

This protocol is performed as an:

■Inpatient ■Outpatient □Community □Ect. ( )

Length of Stay : (What is the length and frequency of hospitalization)

Follow-up will be performed on the day of surgery as well as 2 weeks, 3 months, 1 months and 1 year postoperatively.

Where will study be conducted:

□ Only at WMH □ Community ■ Multicenter ( ■Domestic □ Multinational)

Name of Sponsor / Funding Source:

Not applicable

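### With 60 per group and the planned 20% loss, the 95% confidence interval rule gives about 82% power, not the stated 90%

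*Protocol*

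**What the plan says.** Under Statistical Consideration, the Protocol sets the equivalence limit at 12.8 ODI points, taken from a published minimal clinically important difference. For variability it cites an earlier study in which "the standard deviation of the ODI value at 1 year after decompressive laminectomy was 18.8". From these it concludes: "alpha = 0.05, power = 0.90, two-sided 95% confidence interval, and follow-up loss at 20%, 60 participants are needed in each group".

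The 60 already allows for loss: "Target sample size: 120 subjects (Study group: 60 subjects, Control group: 60 subjects, including 20 % drop-out rate"). The Estimated Accrual entry of the Protocol Abstract repeats this.

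The analysis method under Primary Endpoint sets the decision rule: "Equivalency will be declared if the upper and lower limits of the 95% confidence interval (CI) of the treatment difference value" for 12-month ODI "fall within the pre-defined equivalence margin (+-12.8"). The 95% level thus appears both in the sample-size statement and in the rule that decides the trial.

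**The concern.** An equivalence claim based on a two-sided 95% interval tests each side at 0.025. One based on a 90% interval tests each side at 0.05. The sample-size statement gives alpha as 0.05 and also names a 95% interval. If 0.05 was applied to each one-sided test, the number obtained belongs to a 90% interval and is too small for the rule the Protocol adopts.

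Equivalence is the primary objective. If the trial is underpowered for its own rule, a truly equivalent technique is more likely to give an inconclusive result, and readers would judge that result against a power the design does not have. The mismatch could also invite a later switch to a 90% interval to agree with the sample size, which would double the error rate on each side.

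**Working it through.** **Inputs**

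- Margin δ = 12.8, SD σ = 18.8, loss 20%, stated power 0.90: Statistical Consideration.
- Rule: both limits of the 95% interval within ±12.8: Primary Endpoint.
- Allocation 1:1: Study design.
- Evaluable per group: 60 × 0.8 = 48.
- True difference 0: an assumption, as the Protocol text does not state one. It is the most favourable value.

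**Formulas**

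In the normal approximation, with a₁ the one-sided level and a true difference of 0:

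- n per group = 2 (σ/δ)² (z₁₋ₐ₁ + z₁₋β/₂)². β is halved because both limits must be met.
- Power = 2Φ(δ/SE − z₁₋ₐ₁) − 1, with SE = σ√(2/n).

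The exact figures use two one-sided t-tests, integrating over the distribution of the sample SD.

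**Step 1: reproduce 60**

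2 × (18.8/12.8)² = 4.3145.

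At 0.05 per side (90% interval): 4.3145 × (1.645 + 1.645)² = 46.7, so 47 evaluable and 47/0.8 = 58.75, or 59 randomised. With exact t-tests, 47 gives 89.7% and 48 gives 90.4%. So 48 is the smallest sufficient number, and 48/0.8 = 60, the Protocol's figure.

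**Step 2: apply the stated rule**

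At 0.025 per side (95% interval): 4.3145 × (1.960 + 1.645)² = 56.1, so 57 evaluable and 57/0.8 = 71.25, or 72 randomised. With exact t-tests, 57 gives 89.97% and 58 gives 90.6%, so 58 evaluable and 58/0.8 = 72.5, or 73 randomised.

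**Step 3: power at the planned number**

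With n = 48, SE = 18.8 × √(2/48) = 3.84 and δ/SE = 3.335.

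| Interval | Level per side | Power, normal | Power, exact t |
|---|---|---|---|
| 90% | 0.05 | 90.9% | 90.4% |
| 95% (stated) | 0.025 | 83.1% | 82.0% |

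**Step 4: sensitivity under the 95% rule (exact t)**

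| Evaluable per group | True difference | Power |
|---|---|---|
| 60 (no loss) | 0 | 91.8% |
| 48 | 0 | 82.0% |
| 48 | 2 points | 76% |
| 48 | 3 points | 70% |

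The non-zero differences are illustrations and do not come from the Protocol.

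**The case against.** Several points can be made in the plan's defence.

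- **The 82% is conditional.** It needs the full 20% loss; with no loss, power is 91.8%. This is true, but the Protocol plans for 20% loss and counts it in the 60, so 48 is the number on which its power claim must stand.
- **The source of the 60 is inferred.** A figure after the sample-size statement is not available and may show the calculation. A one-sided 0.025 formula with undivided β comes close: 4.3145 × (1.960 + 1.282)² = 45.3, so 46 evaluable and 58 randomised. How the 60 arose therefore cannot be proved. However, that formula ignores the need to meet both limits, and whichever was used, 48 evaluable under the 95% rule still give 82%.
- **The analysis itself is not settled.** The endpoint is defined as a difference from baseline, but the rule is applied to the 12-month score. The missing-data bullets under General Statistical Analysis also conflict: one imputes missing primary data, another analyses efficacy data without imputation. For a change score with equal SDs at both times (an assumption), power at 48 would be about 59%, 82% or 92% at correlations of 0.3, 0.5 or 0.6. So 82% is the power implied by the Protocol's own sample-size inputs, and the power of the final analysis could differ. That does not rescue the 90%, which the Protocol derives from those same inputs.
- **The error is on the safe side.** The 95% rule is the stricter one, so a positive equivalence conclusion is unaffected. This stands. The harm is a misstated power and a higher chance of an inconclusive trial.

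**Conclusion.** The concern holds. The stated power, interval level and sample size cannot all be true. The shortfall is about 8 percentage points of power, so the type II error is about 18% instead of 10%, nearly double. In patients, it is 12 to 13 per group. This is well beyond rounding or the choice between normal and t-based formulas.

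The result assumes SD 18.8, 48 evaluable per group, an unadjusted comparison of 12-month scores and a true difference of zero. Any true difference other than zero lowers the power further.

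**What to change.** Keep the 95% interval rule and correct the sample-size sentence, for example: *60 per group (48 evaluable after 20% loss) give about 82% power for the two-sided 95% confidence interval to lie within ±12.8, assuming SD 18.8 and no true difference.* Remove the 90% claim. The cost is one sentence and a less favourable stated power; no patients are added.

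If 90% is to be kept, there are two routes:

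- **Enlarge the trial** to 73 per group: 146 in total, 26 more than planned. The normal approximation gives 72 per group, 144 in total.
- **Base the power on a baseline-adjusted analysis.** A baseline to 12-month correlation of about 0.41 reduces the SD to 18.8 × √(1 − 0.41²) = 17.1 and gives 90.3% at 48 per group. The Protocol gives no correlation and specifies no adjustment in its primary rule. This route therefore also changes the primary analysis, and the correlation must be stated as an assumption.

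The interval should not be changed to 90% once outcome data have been seen.

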Before surgery, conduct pre-surgery radiological assessment, clinical physical examination (age, gender) and medical history taking (disease history, surgical history) for these subjects, and check the results of the clinical laboratory tests (CBC, Routine chemistry). Check for complications based on radiological imaging tests (X-ray) before surgery, immediately after surgery (X-ray, MRI or CT), and 2 weeks, 3 months, 6 months and 12 months after the surgery. Perform clinical assessments by conducting questionnaires on VAS, ODI, EQ5D, gait, satisfaction, and POSAS before surgery and 2 weeks, 3 months, 6 months and 12 months after the surgery. Immdiately after the surgery, take measurements on the items related to the surgery (postsurgery bleeding, duration of surgery, hospital stay, Creatine Kinase (CK, CPK) at postoperative day 1) to compare surgery-related items.

- However, if the subject is unable to visit the site at planned dates due to unavoidable reasons (such as safety issues due to COVID-19), non-face-to-face treatment or telephone surveys permitted by the current laws can replace the actual outpatient visit.

Eligibility:

Patients with ≥ grade B lumbar central canal stenosis who agree to undergo one to two segment posterior spinal decompression surgery, those who can be followed up for at least 1 year.

Inclusion Criteria:

1. Ages 20 to 80
2. Patients ≥ grade B lumbar central canal stenosis who agree to undergo one to two segment posterior spinal decompression surgery
3. Those who can be followed up for at least 1 year
4. Subjects who signed the informed consent form on own (if the subject is able) or through a legally authorized representative after fully understanding the details of the clinical trial

Exclusion Criteria:

1. Patients with spondylolisthesis (Meyer grade ≥ II)
2. Those who have had the same segmental surgery
3. Degenerative lumbar scoliosis (Cobb angle > 20°)
4. Cause of the lumbar spinal stenosis is not of degenerative nature or it is caused by lumbar disc herniation
5. Presence of other spinal disorders in the lesions of the lumbar spinal stenosis (e.g. ankylosing spondylitis, spinal tumor, spinal fracture)
6. Psychological disorders (such as dementia, intellectual disability, or drug abuse)
7. Those who have refused to participate in the study
8. Other patients deemed ineligible by the investigator to participate in the clinical trial

Treatment Plan:

- Surgical Method

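### The Schedule of Activities leaves the walking questionnaire blank before surgery, although the protocol text analyses walking as change from baseline

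*Protocol*

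**What the plan says.** Three parts of the protocol text call for walking to be measured before surgery.

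- **Study design:** "Perform clinical assessments by conducting questionnaires on VAS, ODI, EQ5D, gait, satisfaction, and POSAS before surgery", and again at the follow-up visits.
- **Assessment and Analysis of Study Results, Walking time:** values at "postoperative 2, 12, 24, and 52 weeks are compared to the baseline values".
- **Secondary Endpoints:** the clinical outcomes include "walking distance and time, satisfaction after surgery". The analysis is a repeated measures ANOVA of "the differences from the baseline values to the postoperative values and differences in the pattern of change between the two groups", with t-tests at single time points.

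The Schedule of Activities has six visits: "Visit week | -4~0weeks | 0 day | 2 weeks | 12 weeks | 24 weeks | 52 weeks". Its row "Walking questionnaire" is empty at Visit 1 (screening) and Visit 2 (day 0), and marked at Visits 3 to 6.

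Two in-hospital measurements also appear in the text and not in the table. The VAS entry says that "the degree of pain in the surgical site (Postoperative Day 1 or Day 2) is also investigated using VAS", and the entry on other surgery-related outcomes says that "postoperative Day 1 creatine kinase (CK, CPK) are also evaluated".

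**The concern.** A schedule of activities is the table that site staff can be expected to work from, and this trial recruits at three sites. Nothing in the protocol says whether the table or the text prevails. If staff follow the table, the walking questionnaire is first given two weeks after surgery.

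A patient's walking ability before decompression cannot be measured afterwards. The protocol also allows Visits 1 and 2 to take place together, so there may be no later preoperative contact at which to notice the gap. At stake is the baseline for a secondary endpoint that describes function directly in patients with spinal stenosis.

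**Working it through.** The plan states no figure on this point, so the check compares the table with the text, row by row.

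**Step 1. The questionnaire rows of the Schedule of Activities.**

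| Row | Visit 1, screening | Visit 2, day 0 | Visits 3–6 (2, 12, 24, 52 weeks) |
|---|---|---|---|
| ODI | marked | blank | all four marked |
| EQ-5D | marked | blank | all four marked |
| VAS | marked | blank | all four marked |
| Walking | blank | blank | all four marked |
| Other (satisfaction, daily activities, POSAS) | blank | blank | all four marked |

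The table does show baseline questionnaires where they are intended. The walking row instead follows the pattern of the instruments that make sense only after an operation.

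**Step 2. What the walking analysis needs.** The changes are week 2 − baseline, week 12 − baseline, week 24 − baseline and week 52 − baseline. All four use the same preoperative value. If it is not collected, 4 of 4 changes are undefined, and so is the part of the ANOVA that measures change from baseline. The between-group comparisons of postoperative values at 2, 12, 24 and 52 weeks need no baseline, so 4 of 4 of those remain. Because the groups are randomised, they remain valid comparisons, without the within-patient reference.

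**Step 3. Whether the missing-data rules repair it.** General principles of analysis prescribes last observation carried forward for secondary efficacy endpoints. A baseline has no earlier observation to carry forward. Handling of analysis sets says that missing efficacy data are analysed without imputation. That leaves no change score. Neither rule helps.

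**Step 4. The in-hospital items.** The laboratory row is marked at screening only, with CPK named in its footnote. The VAS row is blank between screening and 2 weeks. No column lies between day 0 and 2 weeks. The schedule also has no rows for incision size, drainage, operative time or hospital stay, all of which the text requires. The Day 1 creatine kinase and the early surgical-site VAS are therefore perioperative items that the table does not list. They are not time points that it denies.

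**Step 5. The primary endpoint.** ODI is marked at screening and at 52 weeks. It is not affected.

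**The case against.** The strongest reply is that the text already asks for the measurement. Study design says that all questionnaires are done before surgery and names gait among them, and the Walking time entry presupposes a baseline. A site that reads the whole protocol would collect it. This stands as far as it goes: the assessment is not absent from the plan, but one part of the plan contradicts another. It also rules out the stronger claim, which a reader might infer, that none of the 120 patients will have a baseline walking value. That would follow only if every site ignored the text, and the documents give no reason to expect it.

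The Study design sentence is also loosely written, since it asks for satisfaction and scar scores before surgery too, so it could be discounted as evidence of intent. The contradiction does not depend on it: the Walking time entry and the Secondary Endpoints analysis each need a baseline.

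A reader might also conclude that the walking, creatine kinase and wound-pain endpoints cannot be computed at all. For walking, only the change from baseline would be lost. For the other two, the text states the measurement and the case report form could capture it. The early surgical-site VAS is an observation item without an analysis of its own.

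A reader might suspect, too, that the choice of Day 1 or Day 2 lets the pain reading fall on different days in the two groups. The window is the same for both groups, and nothing in the documents indicates that its use would differ.

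Finally, the table's footnote markers run 1, 2, 4 and 5, so a note may have been lost in reading the file. That calls for some caution about the in-hospital items. It does not change the walking row, whose cells are clear.

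**Conclusion.** The walking row of the Schedule of Activities is wrong as written, because it contradicts the Study design text, the Walking time entry and the Secondary Endpoints analysis. At a site that follows the table, the preoperative walking value and all four change-from-baseline contrasts would be lost beyond repair. Postoperative between-group comparisons of walking would survive, and the equivalence conclusion on ODI would not be touched. The point should be corrected, but it does not threaten the main result.

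The conclusion assumes that the walking questionnaire in the table is the instrument meant by gait in Study design and by walking time or distance elsewhere, and that the table has been read correctly from the file. How many patients would be affected cannot be derived from the documents, since it depends on how sites use the table.

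The missing slots for Day 1 creatine kinase and the early surgical-site VAS are a secondary matter of reconciliation. The documents do not support treating them as contradictions of equal weight.

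**What to change.** Mark the walking questionnaire at Visit 1 (screening) in the Schedule of Activities, so that it matches the ODI, EQ-5D and VAS rows and the text. Where Visits 1 and 2 are combined, the form should be completed before the operation.

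In the same revision, add an in-hospital postoperative column between day 0 and 2 weeks. Enter in it the Day 1 creatine kinase and the Day 1 or Day 2 surgical-site VAS, as the text already states them.

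The cost is a correction to one table and, at any site that has worked from the table alone, one more short form at screening. The text already requires all of these measurements, so the protocol's burden on patients does not grow. The change helps only patients who have not yet had surgery.
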